### Procedures

At baseline, demographic information and disease history will be collected via interview. At each measurement interval (i.e., baseline, 6 months, 1 year, 1.5 years and 2 years), (1) co-morbidity data will be collected using a modified version of the Comorbidity Questionnaire, a reliable and valid instrument that offers practical advantages over medical record based assessments [17]; (2) depression will be assessed using the Geriatric Depression Scale [18,19]; and (3) medication data (i.e., drug name, dose, frequency, levo-dopa equivalence) will be collected using a customized form. In addition, a suite of standardized instruments will be employed at each measurement interval to capture participant physical function, mobility, physical activity, and quality of life. The instruments have been selected for their strong psychometric properties and collective representation of ICF domains (Table 1 and Figure 1)

**Table 1 T1:** Battery of Outcome Measures

ICF Disablement Construct	Outcome Variable
Body Structure and Function	
	MDS-UPDRS Sections I, III

Activity	
	6 Minute Walk Test
	9 Hole Peg Test
	Berg Balance Scale
	Freezing of Gait Questionnaire
	Functional Gait Assessment
	Gait Speed (10 meter walk)
	MDS-UPDRS Section II
	Timed Up and Go

Participation	
	Ambulatory Activity
	PASE
	PDQ-39

MDS-UPDRS = Movement Disorders Society-Unified Parkinson Disease Rating Scale; PASE = Physical Activity Scale for the Elderly; PDQ-39 = Parkinson Disease Questionnaire - 39

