### Statistical Analysis Plan

Confidence intervals, means, standard deviations and frequency distributions will be calculated for all measures. Corrections for multiple comparisons will be used to control for increased type I statistical error risk. Effect sizes and post hoc power will be calculated when appropriate. All analyses will be performed with SPSS 16.0 (SPSS Inc).

To address study objective 1, disablement trajectory will be characterized using interval and point estimators of each outcome measure. In addition, survival analyses will be utilized to examine the time to reach operationally defined mobility thresholds (i.e., limited community ambulatory gait speed, assistance with ADL's, time to recurrent falls). This approach will allow us to characterize the distribution of time-to-event data, to test for differences between subgroups (i.e., exercise history, disease severity, disease sub-type, age, number of cormorbidities), and to utilize regression models to analyze complex influences of covariates on time to event data[16].

To address study objective 2, multiple regression analyses will be conducted to identify those factors associated with progression of disability. Assessments for violation of assumptions will be made, including analyses of normality of the residuals and linearity of the continuous variables[16]. As needed, potentially more potent contributors will be used to define subgroups within the sample (e.g., exercisers vs. non-exercisers; physically active vs. sedentary), and analyses of variance will be used to evaluate between- and within-group differences in disablement change.

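### The follow-up comparison of exercisers with non-exercisers is specified as analysis of variance without covariates, so baseline differences in disease and treatment can appear as an exercise effect

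*Protocol article*

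**What the plan says.** Under Statistical Analysis Plan, the protocol article addresses objective 2 in two steps. First, "multiple regression analyses will be conducted to identify those factors associated with progression of disability". Second, "As needed, potentially more potent contributors will be used to define subgroups within the sample (e.g., exercisers vs. non-exercisers; physically active vs. sedentary"), and then "analyses of variance will be used to evaluate between- and within-group differences in disablement change". No covariate is named for the second step.

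For the time-to-event analyses under objective 1, subgroup differences are to be tested by "exercise history, disease severity, disease sub-type, age, number of cormorbidities", and the plan will also "utilize regression models to analyze complex influences of covariates on time to event data".

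Under Procedures, "At baseline, demographic information and disease history will be collected via interview". At every visit comorbidity is recorded, and "medication data (i.e., drug name, dose, frequency, levo-dopa equivalence) will be collected using a customized form". Hoehn and Yahr stage is established at entry (Participants and Recruitment), and MDS-UPDRS Section III is scored at each visit (Measure of Body Structure and Function).

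Power and Sample Size Estimates expects 150 participants at two years and, by its rule N ≥ 50 + 8X, allows up to 12 predictors. It does not list them.

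**The concern.** This is an observational cohort, so nobody is assigned to exercise. Entry spans Hoehn and Yahr stages I to IV and ages from 40 upward. People with milder disease, fewer comorbidities or younger age may find it easier to exercise and may also decline at a different rate. The plan itself puts severity, age and comorbidity beside exercise history as factors worth examining for time to event.

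An analysis of variance by group does not separate these influences from exercise. The same holds if it is run as a repeated-measures analysis: the group-by-time term is then just as unadjusted. The preceding regression can adjust, but its adjustment does not carry over when a contributor is picked out, turned into groups and tested again. Fixing the groups at baseline would not help either, because the imbalance is already present then. The promised corrections for multiple comparisons address chance findings, not bias.

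The article's abstract presents the evaluation of exercise and physical activity as a preliminary step toward a randomised trial. A simple group difference is easy to quote, and readers may take it for the exercise effect.

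**Working it through.** **The plan's own figures.** 260 × 0.75² = 146.25, close to the stated 150. The predictor rule gives 50 + 8 × 12 = 146 and (150 − 50)/8 = 12.5, so 12 predictors are supported. These figures hold.

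**Inputs for the bias.** The documents give no group sizes, no baseline imbalance and no correlation with change. All of the following are therefore assumptions:
- 150 completers, split 75/75 or 50/100;
- no true exercise effect;
- d, the standardised group difference in a baseline confounder, from 0.2 to 0.8;
- r, the within-group correlation of that confounder with change, from 0.2 to 0.5;
- a two-sided 5% test without multiplicity correction.

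**Formulas.**
- Bias of the unadjusted difference = d × r, in SDs of change.
- SE = √(1/n₁ + 1/n₂) = √(2/75) = 0.163 for 75/75.
- Rejection rate = 1 − Φ(1.96 − bias/SE) + Φ(−1.96 − bias/SE).

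**Results for 75/75.**

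| d | r | Bias (SD) | Bias/SE | Rejection rate |
|---|---|---|---|---|
| 0.2 | 0.2 | 0.04 | 0.24 | 5.7% |
| 0.3 | 0.3 | 0.09 | 0.55 | 8.5% |
| 0.5 | 0.3 | 0.15 | 0.92 | 15.1% |
| 0.5 | 0.5 | 0.25 | 1.53 | 33.4% |
| 0.8 | 0.5 | 0.40 | 2.45 | 68.8% |

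With a 50/100 split the range is 5.6% to 64%.

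**Simulation check** (4,000 data sets each, 75 per group). ANCOVA here adjusts for the measured confounder.

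| d | r | ANOVA rejects | ANCOVA rejects |
|---|---|---|---|
| 0.3 | 0.3 | 8.4% | 5.5% |
| 0.5 | 0.3 | 15.0% | 5.3% |
| 0.5 | 0.5 | 33.8% | 4.4% |

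The ANCOVA bias was 0.00 SD in all three settings. The simulation assumes that the confounder is fully measured and linearly related to change, so it shows the best that adjustment can do.

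**Does the adjusted model fit the sample?** Count the terms: group 1, age 1, severity 1 (or 3 if the four Hoehn and Yahr stages are categories), disease duration 1, levodopa-equivalent dose 1, comorbidity count 1, and four sites 3.
- Without the baseline outcome: 9 to 11 predictors, needing 50 + 8 × 9 = 122 to 50 + 8 × 11 = 138.
- With the baseline outcome: 10 to 12 predictors, needing 130 to 146.

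Both fit the expected 146 to 150, the largest version only just.

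**The case against.** The strongest reply is that the analysis of variance is not the main exercise analysis. Objective 2 is led by multiple regression, and the objective expressly covers exercise and physical activity. The group comparison follows only as needed, and exercisers versus non-exercisers is one example. The article is also a condensed text: it does not exclude covariates, and covariate lists are commonly left to a fuller plan. This stands in part. It limits the point to one follow-up step and rules out any complaint about a missing covariate list. It does not remove the point, because the article names a method for that step, and that method as named is unadjusted.

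A reader might infer that the plan as a whole ignores confounding, or that levodopa equivalence is recorded but never used. The documents do not support either reading. The regression predictors are not listed, so levodopa equivalence may be among them. The closed list in the survival section covers subgroup tests only, and the same sentence provides regression with covariates. A reader might also infer that the group difference will set the effect size of the later trial. The article does not say so.

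Three further objections stand as cautions:
- The magnitude is wholly assumed, and at the lower end there is almost no inflation. Multiplicity correction would lower the rejection rates, though not the bias.
- Adjusting change for the baseline outcome in self-selected groups is debatable (Lord's paradox).
- If exercise began before enrolment, baseline severity and dose may partly result from it, and adjusting for them could remove part of what is sought.

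**Conclusion.** The point holds for the conditional group contrast, and for that only. As specified, the comparison of self-selected groups on disablement change is unadjusted, although the lead analysis for the same objective can adjust and the relevant baseline data are collected. The direction and size of the bias cannot be known from the documents. Over the assumed ranges it is 0.04 to 0.40 SD of change, with rejection of a true null in about 6% to 69% of studies at an uncorrected two-sided 5% level. If the groups turn out similar at baseline, the harm is small, but the step as written offers no protection if they do not. The change is worth making before analysis. It does not call into question the regression, the survival analyses or the sample size.

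**What to change.** Estimate the group contrast as a term in the objective 2 multiple regression, or by ANCOVA. Prespecify the baseline covariates: age, Hoehn and Yahr stage or MDS-UPDRS Section III, disease duration, levodopa-equivalent dose, comorbidity count and site. Where Section III is itself the outcome, use Hoehn and Yahr stage as the severity covariate.

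Use baseline rather than follow-up dose, since a change in dose during follow-up may be a consequence of progression. Show the result with and without the baseline outcome as a covariate. Present any unadjusted analysis of variance as descriptive only.

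The cost is wording plus 9 to 11 of the 12 predictors allowed (10 to 12 with the baseline outcome), which leaves little room for other terms. It assumes that disease duration can be taken from the disease history interview. If active versus sedentary is defined by the step monitor, only a sub-group of participants wears it. The sample is then smaller, and the covariate list must be shortened to match. Since baseline severity and dose may partly reflect earlier exercise, and unmeasured differences remain, report the adjusted contrast as an association.

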### Data management

The multicenter protocol will rely on a web-based system of data input into a central database. The system will feature multi-tiered security-protected access and will conform to HIPAA security policies. Stored data will be backed up daily. Authenticated investigators will have access to the dataset from any Internet access point.

Prior to data collection, study personnel at each site will review a standard operating procedures (SOP) protocol manual and will rate two standardized persons with PD, who will have been filmed performing the battery of physical performance tests. Study personnel and site specific ratings will be evaluated by the data management team to insure their accuracy and consistency.

At each measurement interval, data will be collected on paper forms and entered into the web-based data entry portal by a specific individual at each site. The data management team subsequently will confirm the accuracy of data entry for every third participant by comparing electronic data with the original hard copy data. In addition, the team will select files at random for similar review. Researchers at each site will be notified of any discrepancies or incomplete data.

## Discussion

Tertiary prevention is an important component of contemporary healthcare for individuals with degenerative disease. Yet only recently has attention been given to the evolution of disability among persons with PD[13,48-51]. Such studies, however, while valuable, have been limited by cross-sectional designs and limited scope of disablement. To our knowledge, our proposed study is novel for its longitudinal examination of the natural trajectory of disablement, exercise habits, and physical activity in a cohort of persons with PD. In this context, data collected in the study will provide a foundation for future exercise intervention research. Not only will the study characterize disablement using a broad spectrum of measures, it also has the potential to identify factors that might influence, either positively or negatively, the rates at which persons with PD experience decline in mobility and quality of life.
